### Subject population and setting

A total of 10,935 patients were screened, and 600 eligible individuals were recruited to participate. All participants were patients at three primary care clinics in the Philadelphia metro area. The three clinics in this study are all FQHCs serving traditionally underserved populations, including many low-income and uninsured patients. In addition to providing primary care, the FQHCs offer supportive services such as case management, health education, and prevention using an interdisciplinary approach. The study primarily included adults over the age of 21, but older adolescents (i.e., 18–21 years) were not excluded. All three of the FQHCs are located in neighborhoods of Philadelphia that have greater minority representation than is found for the city as a whole. Our sample was approximately 82 % Black, 7 % White, and 12 % other races. About 8 % were Hispanic and approximately 45 % of our participants were women; the average age was 40. About 30 % were employed either full-time or part-time, 66 % were never married, 11 % were married or cohabitating, and 75 % had at least a high school diploma or equivalent. There was a fairly even split of primary substance use; 35 % of participants primarily used alcohol, 38 % marijuana, and 27 % other substances.

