### Power for the primary hypotheses

Power analyses are based on the sub-group contrasts identified for each of the primary hypotheses. The analyses are based on a two sided alpha of .0125 (.05/4 outcome variables–number of treatment sessions attended, urinalysis-confirmed abstinence, days of self-reported drug use, and cost of acute care), an estimated correlation of .5 between the repeated measurements where applicable, and a 20 % attrition rate by month 12. Power calculations were based on Diggle, Heagerty, Liang, and Zeger [58] for the mixed effects models, Hedeker, Gibbons, and Waternaux [59] for the GEE models, and Cohen [60] for the cost-related hypotheses. With a sample size of 100 per condition in the illicit drug sub-group, we will have 80 % power to detect moderate effects of the intervention (*d* = .5) for the mixed effects models and cost-related analysis and 80 % power to detect a 20 % difference between the two groups for the GEE model. With a sample size of 200 per condition in the alcohol/marijuana sub-group, we will have 80 % power to detect smaller effects of the intervention (*d* = .25–.30) for the mixed effects models and cost-related analysis and 80 % power to detect smaller differences (13–15 %) between the two groups for the GEE model.

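### The detectable effects for the two sub-groups cannot come from one calculation, and d = .25–.30 does not have 80% power for the cost analysis in the alcohol/marijuana sub-group

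*Protocol article*

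**What the plan says.** All figures are in the Protocol article, section Power for the primary hypotheses, unless noted.

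- Error rate: "The analyses are based on a two sided alpha of .0125", which is .05 shared equally among four outcomes (sessions attended, urine-confirmed abstinence, days of use, cost of acute care).
- Other inputs: "an estimated correlation of .5 between the repeated measurements where applicable" and "a 20 % attrition rate by month 12".
- Illicit drugs: "With a sample size of 100 per condition in the illicit drug sub-group", the section says "we will have 80 % power to detect moderate effects of the intervention", given as d = .5. The GEE model is said to detect a 20% difference.
- Alcohol/marijuana: "With a sample size of 200 per condition in the alcohol/marijuana sub-group", it claims 80% power for d = .25–.30, and for 13–15% in the GEE model.
- Each d is stated for the mixed models and the cost-related analysis together. The cost calculation is credited to a different source from those for the mixed and GEE models.

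The data analysis section sets the models. H1 compares sessions at 3, 6, 9 and 12 months and names no baseline covariate. H2 adds the baseline value of the outcome as a covariate. The power section does not say whether the mixed-model effect is a time-averaged difference or a slope, or whether baseline is adjusted for.

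**The concern.** Only the sample size changes between the two sub-groups; alpha, correlation, attrition and power are common. The two detectable effects should therefore differ by the square root of 2. They differ by a factor of 1.67 to 2.0. In addition, a single d is attached to two kinds of analysis that do not have the same precision. The repeated-measures correlation helps a model of four visits, but gives nothing to a comparison of one cost figure per patient.

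These sub-group contrasts are what the primary hypotheses were powered on. A reader who takes d = .25–.30 at face value would think the alcohol/marijuana cost comparison, and at the lower end the H1 comparison, more sensitive than it is, and could read too much into a null result.

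**Working it through.** **Inputs.** Two-sided alpha .0125, so z = 2.498. Power 80%, so z = .842. The sum is 3.339 (from unrounded values). Per condition: 100 and 200 as stated, or 80 and 160 if the 20% lost contribute nothing. Four follow-up visits, correlation .5.

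**Formulae.** Detectable d = 3.339 × √(2V/n). Power = Φ(d/√(2V/n) − 2.498). V is the variance of the analysed quantity relative to a single measure:

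- one measure per patient (cost): V = 1
- mean of four visits, compound symmetry (assumed): V = (1 + 3 × .5)/4 = .625
- the same with a baseline covariate also correlated .5: V = .625 − .25 = .375
- linear slope over the four follow-ups, expressed as the change from first to last visit: V = .90

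**Step 1: consistency, with no choice of V.** For fixed V and attrition, d is proportional to 1/√n. From .5 at 100 per condition, 200 gives .5/1.414 = .354. From .25–.30 at 200, 100 gives .354–.424. Rounding does not close the gap, since .424 would round to .4. Nor does counting attrition in the illicit sub-group only: √(200/80) = 1.58, still below .5/.30 = 1.67. The GEE figures do obey the rule: 20%/1.414 = 14.1%, inside the stated 13–15%. The anomaly is confined to the d values.

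**Step 2: trying to reproduce the stated d values.** Each range runs from no loss to full 20% loss.

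| Analysis | V | Illicit (100 to 80); stated .5 | Alcohol/marijuana (200 to 160); stated .25–.30 |
|---|---|---|---|
| Cost, single measure | 1 | .472–.528 | .334–.373 |
| Mean of 4 visits, no baseline | .625 | .373–.417 | .264–.295 |
| Mean of 4 visits, baseline covariate | .375 | .289–.323 | .204–.229 |
| Slope over 4 visits | .90 | .448–.501 | .317–.354 |

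No row gives both stated figures. The rows that give about .5 (cost, slope) do not give .25–.30. The unadjusted time-averaged row, which supports most of .25–.30, gives about .4 for illicit drugs.

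**Step 3: power at the stated d.**

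- Cost, alcohol/marijuana. At 200 per arm √(2/200) = .1. For d = .25, Φ(2.5 − 2.498) = 50%; for d = .30, Φ(3.0 − 2.498) = 69%. At 160 per arm: 40% and 57%.
- Cost, illicit, d = .5: 85% at 100 and 75% at 80 (exact t-test 84% and 74%).
- H1 mixed model, alcohol/marijuana, V = .625. For d = .25, 75% at 200 and 63% at 160; for d = .30, 90% and 82%. With graded dropout of 5, 10, 15 and 20% across the visits (assumed), d = .25 has 70% and the 80%-power effect is .275.
- Time-averaged mixed model, illicit, d = .5, V = .625: 98% at 100 and 93% at 80. With the same graded dropout the 80%-power effect is .389.
- H2 with its baseline covariate, alcohol/marijuana, d = .25, V = .375: 94% at 200 and 88% at 160.

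**The case against.** The strongest reply is that the article does not state the contrast and points to sources for the method. A four-visit slope with 80 completers gives d = .501, so .5 can be reached from the stated inputs. The figure also covers the cost analysis, where it is about right, and may be a rounded joint value for the weaker of the two. The lower end, .25, may be meant for the baseline-adjusted H2 model, and H1 leaves room for further covariates. A null result would in any case be read from its confidence interval, and recruitment is complete.

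Much of this stands. A reader might infer that .5 is simply wrong, or that the illicit-drug contrast is underpowered. The documents support neither. A reader might also infer that .25 is out of reach for every mixed model. The covariate planned for H2 refutes that, and an AR(1) correlation with no loss would give 84% at .25, although the power section mentions neither.

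Two things remain. Each reading that rescues one figure breaks the other: the slope gives .32–.35 for alcohol/marijuana, and baseline adjustment moves the illicit figure to .29–.32. And no single-measure cost comparison at 160–200 per arm has 80% power at .25–.30. Were cost instead modelled as four repeated measures with correlation .5, the unadjusted time-averaged row would apply, and .25 would still fall short.

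**Conclusion.** The point holds in limited form. The pair d = .5 and d = .25–.30 cannot follow from one method and the shared inputs.

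- **Cost, alcohol/marijuana:** the clearest error. About .33–.37 is needed, and power at the stated effects is about 40–69%. This assumes one cost measure per patient, consistent with the correlation being applied only where applicable.
- **H1, alcohol/marijuana:** the upper end, .30, is supported; .25 has about 63–75% power. This assumes a time-averaged contrast, compound symmetry and no baseline adjustment.
- **H2, alcohol/marijuana:** .25 is reachable with the planned baseline covariate.
- **Illicit drugs:** .5 fits the cost analysis (.47–.53) and is conservative for a time-averaged mixed model without baseline adjustment (.37–.42). This is inconsistent reporting, not a shortage of power.

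It is tempting to add that the illicit sub-group enrolled is smaller than planned. The section on the subject population reports that "There was a fairly even split of primary substance use", with 27% mainly using substances other than alcohol or marijuana. That would be 162 of 600, or 81 per arm (about 65 after 20% loss), and a time-averaged detectable d of .42–.46. But the data analysis section describes this sub-group by use of harder drugs, not by primary substance, so its size may be larger. The figure is an assumption, not the enrolled size.

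**What to change.** Rewrite the power paragraph. State whether the mixed-model contrast is time-averaged or a slope, and whether baseline is adjusted for. Then give detectable effects by analysis from one formula, saying how attrition enters:

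- Cost: about .47–.53 (illicit) and .33–.37 (alcohol/marijuana).
- H1, if time-averaged without baseline adjustment: about .37–.42 and .26–.30.
- H2: its own baseline-adjusted figures; under the assumptions above, about .29–.32 and .20–.23.

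Drop .25 for H1, and replace .25–.30 for cost. If values at the enrolled illicit sub-group size are added, label them as resting on the assumption that the 27% primarily using other substances form that sub-group (about 81 per arm). The cost is the wording of one paragraph. Design, conduct and analyses do not change; some stated effects become smaller and others larger.

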### Intervention procedures

All participants were screened for risky substance use prior to being invited to enroll in the study. Eligible participants consenting to the study were assigned to BI/RT or BI/RT+ via a block randomization procedure. Half of the patients identified with risky substance use received BI/RT and half received BI/RT+. Research assistants were responsible for assigning participants to conditions using a website programmed with the allocation sequence created by the study’s statistician. Participants, BHCs delivering the intervention, and research assistants were not blinded to group assignment.

In both conditions, all counseling sessions were digitally audio-recorded and securely stored in order to complete supervision and intervention integrity analyses. Throughout the trial, a clinical supervisor and expert in SBIRT reviewed 1 to 2 randomly selected sessions for each BHC each month and provided at least bi-weekly supervision with BHCs to (a) review the BI/RT or BI/RT+ content covered in meetings, (b) reinforce the BHCs’ adherence to the protocol, (c) discuss any protocol breaks that occurred in prior patient meetings, and (d) address any therapeutically relevant issues that might be occurring (e.g., new problems, ethical issues).

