#### **Primary H3**

BI/RT+ will have positive net social benefits relative to BI/RT alone.

As described above, we will measure social benefits (e.g., downstream medical costs, reduced crime) and costs related to the interventions. We will then test whether marginal costs, marginal benefits, and net benefits of the interventions are different than zero.

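### The 80% power stated for the cost analysis at d = .25–.30 in the alcohol/marijuana sub-group fits the four-visit mixed models, not a single two-group cost comparison, where it is about 50–69% before attrition

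*Protocol article*

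**What the plan says.** The section on power for the primary hypotheses fixes the inputs. On the error rate: "The analyses are based on a two sided alpha of .0125", which is .05 divided by four outcomes. The last two of those outcomes are "days of self-reported drug use, and cost of acute care". The section assumes a correlation of .5 between repeated measurements where that applies, and 20% attrition by month 12. It names three different sources for its calculations: one for the mixed models, one for the GEE models and one for the cost hypotheses.

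It then gives results by sub-group. For illicit drugs, 100 per condition is said to give 80% power at d = .5 for both the mixed models and the cost analysis. The larger sub-group follows: "With a sample size of 200 per condition in the alcohol/marijuana sub-group", the article says, "we will have 80 % power to detect smaller effects of the intervention", and again one range of d covers both kinds of analysis: "smaller effects of the intervention (*d* = .25–.30) for the mixed effects models and cost-related analysis".

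The hypothesis behind the cost analysis, Primary H3, reads "BI/RT+ will have positive net social benefits relative to BI/RT alone". The short text under it says that marginal costs, marginal benefits and net benefits will each be tested against zero. It names no model, no repeated cost measure and no baseline covariate.

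**The concern.** A mixed model over four follow-ups gains precision by averaging correlated measurements. A single comparison of costs between two groups does not. One range of d at one sample size is therefore unlikely to be the 80% limit for both, and the article itself takes the two calculations from different sources.

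H3 is one of three primary hypotheses. A reader who trusts the sentence may take a null cost result as good evidence against effects of .25 to .30, when the chance of detecting them could have been near even. It is also unclear which cost quantity the figure refers to: the alpha split names one, and H3 lists three others.

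**Working it through.** **Inputs, all from the power section.** Two-sided alpha .0125, so z = 2.498. Power 80%, so z = .842. Sum 3.339. Alcohol/marijuana: n = 200 per condition, or 160 if the full 20% is lost. Correlation .5 where measures repeat. Follow-ups at 3, 6, 9 and 12 months (follow-up procedures section). Allocation is 1:1.

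**Formula.** Detectable d = 3.339 × √(2f/n). For a single comparison f = 1. For the mean of m equally correlated visits f = (1 + (m − 1)ρ)/m.

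**1. The article's own range, mixed models.** f = (1 + 3 × .5)/4 = .625.
- n = 200: 3.339 × √(.625 × 2/200) = .264
- n = 160: 3.339 × √(.625 × 2/160) = .295

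This is the stated .25–.30.

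**2. Cost as a single comparison, f = 1.**
- n = 200: 3.339 × √(2/200) = .334
- n = 160: 3.339 × √(2/160) = .373

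**3. Power at the stated effects.** The normal approximation is Φ(d√(n/2) − 2.498); the noncentral t is alongside.

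| n per condition | d | d√(n/2) | Normal | Noncentral t |
|---|---|---|---|---|
| 200 (no loss) | .25 | 2.500 | 50.1% | 49.7% |
| 200 | .30 | 3.000 | 69.2% | 68.8% |
| 180 (10% average loss) | .25 | 2.372 | 45.0% | 44.6% |
| 180 | .30 | 2.846 | 63.6% | 63.2% |
| 160 (all 20% lost) | .25 | 2.236 | 39.7% | 39.3% |
| 160 | .30 | 2.683 | 57.4% | 56.8% |

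For 80% power the completers needed per condition are 2 × (3.339/d)²: about 357 at d = .25 and 248 at d = .30.

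**4. Illicit-drug sub-group, d = .5, f = 1.**

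| n per condition | Detectable d | Noncentral t power at d = .5 |
|---|---|---|
| 100 | .472 | 84.4% |
| 90 | .498 | 79.6% (normal 80.4%) |
| 80 | .528 | 73.7% |

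So d = .5 lies within the range of the cost limit. For the mixed models it is conservative (.373 with 100, .417 with 80).

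**5. Internal check.** For one and the same test, alpha and loss rate, detectable d scales with 1/√n. If d = .5 is the cost limit at 100 per condition, the limit at 200 is .5/√2 = .35, not .25–.30.

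**The case against.** The strongest reply is that the article never states the cost model. Service use is recorded at every follow-up, the correlation is applied where relevant, and the Data analysis section allows covariates for precision.
- Quarterly costs with correlation .5 would give 81.5% power at d = .30 with 160 per condition, but only 74.7% at d = .25 even with 200.
- A baseline covariate with an assumed correlation of .5 (f = .75) would give 83.3% at d = .30 with 200 and 72.6% with 160; at d = .25 it gives 65.1% and 53.4%.
- Both together (f = .625 − .25 = .375) would cover the range: 3.339 × √(.375 × 2/200) = .20, and .23 with 160. That stacks two assumptions, and its limit is not the range the article gives.

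This stands as a reason to ask which model was meant. It does not rescue the sentence as written, because H3 describes none of these models and the power section sources cost separately.

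Three further objections limit the point, and all stand.
- The 39–57% figures assume that everyone lost contributes no cost data. Attrition is cumulative to month 12 and interim visits exist, so this is the worst case.
- A reader might infer that the illicit-drug cost figure is also wrong. At 10% average loss it has about 80% power, so it is not.
- A reader might infer that power is given for an outcome and sub-groups that H3 does not analyse. The documents do not support this. Acute care cost may be part of the downstream medical costs in H3. The power section refers to sub-group contrasts for every primary hypothesis, and the brief H3 text does not say that the whole sample will be used instead.

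**Conclusion.** The stated 80% power for cost at d = .25–.30 in the alcohol/marijuana sub-group does not follow from the article's own inputs if cost is a single unadjusted two-group comparison. Power is then about 50–69% with no loss and 39–57% with full loss, and the detectable effect is .33 to .37. The shortfall does not depend on how attrition is handled. The range matches the mixed models and appears to have been carried over, although the article does not show how it arose.

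The illicit-drug figure is borderline: about 84%, 80% and 74% power at 0%, 10% and 20% loss. The cost outcome in the alpha split and the quantities in H3 carry different labels and need reconciling; that is an inconsistency, not proof that the wrong outcome was powered. Nor does the point show that the trial was too small for its mixed-model hypotheses. It is a stated power figure to correct, with no effect on conduct.

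**What to change.** - In the alcohol/marijuana sentence, separate cost from the mixed models and give its detectable effect as d of about .33 (200 per condition) to .37 (160).
- In the illicit-drug sentence, give about .47 to .53 for cost, depending on attrition.
- If a repeated-measures or baseline-adjusted cost model was intended, state it with its assumed correlation and give the power for that model instead.
- Reconcile the fourth outcome in the .05/4 split with the three quantities tested under H3, and give power for the H3 contrast that will actually be tested. If that is the whole sample (an assumption; 600 randomised, so 300 per condition), detectable d is 3.339 × √(2/300) = .27. After 20% attrition it is 3.339 × √(2/240) = .305, or about .31 with the noncentral t.

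The cost is a few sentences of text. Recruitment is complete and the economic analysis is described as still to come, so the correction can be made before its results are interpreted.

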## Discussion

The research described here is designed to make important contributions to the substance abuse treatment field and will address practical scientific questions that could have direct bearing on the use of SBIRT in of primary care practices. We will examine whether an expanded brief intervention in a primary care setting has additional value over traditional SBIRT alone.

The expanded BI/RT+ intervention is promising and may lead to better results because it is designed to help patients resolve ambivalence about engaging in more healthy behaviors, and then support patients as they commit to plans to change. Many patients, particularly those with more problematic use, may not initially feel ready to engage in action steps towards changing their substance use. These patients are likely to benefit from an enhanced, multi-session brief intervention.

The BI/RT+ intervention integrates several innovative features. First, BI/RT+ involves a full 2–6 session MET intervention as opposed to one MI session in traditional SBIRT. The advantage of MET over a single session of MI as a brief intervention is the integration of feedback, the opportunity for patients to try a change strategy and adjust it if it is not working, and to involve significant others in key sessions to shore up motivation and decisions to change [61]. A single session brief intervention may be quite galvanizing towards change and action, but may not be enough to sustain change for particularly problematic substance use. Illicit substance users, particularly those with moderate or severe use, may need more support when preparing to change, and to maintain and follow-through on the decision to enter treatment. Second, BHCs using the BI/RT+ intervention will have a menu of evidence-based options to help patients. The health education toolkit designed for this study provides clinicians with materials that allow them to incorporate various counseling strategies that have been demonstrated to be effective for patients with SUDs, including CBT, MET, and 12-step Facilitation. BHCs can use the toolkit materials to tailor their counseling sessions to meet the patient’s individual needs. Finally, in our enhancements to SBIRT, BHCs engage patients in ongoing telephone monitoring monthly after the patient has completed face-to-face interventions. As addiction has increasingly been conceptualized as a chronic disease [62], the concept of conducting ongoing recovery monitoring and intervening in the case of deterioration has been proposed [63].

Given the mixed results in the current SBIRT literature, this study will also further our understanding of SBIRT’s effectiveness. The results of this study will help shed light on when SBIRT works, for whom, and what intensity is most appropriate for various substances and severities. For example, we may find that BI/RT works well for patients using some substances, but patients using other substances may respond better to the BI/RT+ level of care. Our subgroup analyses will examine whether patients who are using harder illicit drugs (cocaine, heroin, etc.) respond differently to BI/RT and BI/RT+ than patients who are primarily using marijuana or alcohol. We will examine a range of outcomes that are important to patients including substance use, engagement in treatment, and medical and psychosocial functioning. These results will further our understanding of SBIRT’s applications and limitations. Additionally, a strength of this study is that it was conducted in FQHCs with a primarily low-income, Black/African American patient population. Thus this study will provide important information about the effectiveness of these interventions for a traditionally underserved population.

While this study will advance our knowledge about SBIRT, there are a few important limitations to note. First, we did not include a no-treatment control condition where patients receive screening only with no brief intervention. A no-treatment control condition would demonstrate the comparative effectiveness of BI/RT and BI/RT+ and provide a more certain estimate of the true effectiveness of the two brief interventions. We chose not to include a no-treatment condition for ethical reasons. We consider it unethical to identify a patient’s substance use problem and then not provide any services to address the problem. However, this research will enable our team to answer the question of whether providing a BHC the latitude to conduct expanded brief intervention (BI/RT+) at the primary care location yields significantly improved patient outcomes.

A second limitation is the potential for condition contamination. In this study, each BHC provided both BI/RT and BI/RT+. The alternate method would be to assign independent BHCs to each condition. The primary advantage associated with nesting providers across interventions, such that each BHC provides both interventions, is that non-specific provider variables are equalized across conditions. The disadvantage associated with this approach is the increased likelihood of condition contamination or “bleeding,” given that providers are administering both interventions and may introduce methods of one intervention into the other. We have elected to nest BHCs across conditions because: (1) we can identify, specify, and measure “bleeding” more clearly than non-specific provider variables; (2) we can take actions to manage protocol violations; and (3) we can assess the influence of intervention integrity on our dependent measures more readily than we can assess the influence of non-specific provider factors.

A final limitation is that we did not conduct hair analysis and used only urinalysis. Hair testing would have allowed us to obtain a biological measure of substance use covering a longer period of time.

By conducting a large-scale randomized trial in real-world health centers, this study will answer important questions about the effectiveness of expanded SBIRT in primary care settings. Furthermore, our economic evaluation and process evaluation will provide additional context for health systems that are considering implementing brief treatment interventions.
